### Intervention

The targeted intervention was developed in the first part of the trial using qualitative methods [24]. As a first step, we reviewed information provided for rehabilitation patients by the clinics. Patients in rehabilitation clinics and clinical experts from all professions were carefully interviewed using structured and videotaped focus groups and several individual in-depth interviews about the following key issues:Information needs and deficitsRealistic, positive, and negative expectationsConcerns, fears, and worries regarding psychosomatic rehabilitation

As a second step, in an interdisciplinary work group with the Media Center of the Johannes Gutenberg-University Mainz, findings from content analysis were transformed into patient and expert scripts and video format. These were embedded in a website, with a front page showing the reception area of a virtual clinic with patients and experts standing in the entrance hall. Patients can visit the clinic via the reception area by choosing one of the patients or the expert and watching the videos linked to the respective person. The videos contain important information on various aspects of inpatient rehabilitation. The website was developed by the Knowledge Media Institute of the University of Koblenz-Landau.

The goal regarding concept and design was to present the information in an easy-to-understand and appealing format. Users on the IP are primarily addressed by video instead of plain written text. The image-based approach of video film makes it possible to visualize key parts of the rehabilitation process such as therapy groups as well as psychological states like apprehension about the upcoming treatment in a very immediate and personal manner.

According to this approach, the video contents which will be presented on the IP can be divided into two sets. The first set contains videos about four different fictional patients in a semi-documentary, realistic form. The videos are designed in a brief and personal format to deliver information in an emotional and informative way. Users can browse through the patients’ stories, from the history and decision for rehabilitation to treatment and follow-up. Each video refers to a crucial aspect of the rehabilitation process (fear of confiding in group therapy, being separated from the family, etc.). The roles of these patients are performed by professional actors.

The second set of videos consists of explanatory videos with explicit explanations of concepts, terms, therapies, and other relevant aspects of rehabilitation. This information is presented by fictional experts from different occupation groups working in inpatient rehabilitation. The roles of the experts are performed by actors and staff from the study center on the basis of the scripts previously created by the psychologists of the study center. All topics included in the scripts have been reviewed and revised by corresponding experts in two cooperating clinics and the German Statutory Pension Insurance.

The user can freely choose the videos of both sets. Participants of the intervention group will get access to the IP after they have given their informed consent. Access will expire when subjects are admitted to inpatient rehabilitation.

### Control condition

The control group receives no intervention in addition to the usual inpatient rehabilitation preparation (“as usual”). The preparation contains written information about inpatient psychosomatic rehabilitation and a link to the homepage of the respective clinic.

### Assessment

Assessments will be conducted at study inclusion (T0), two weeks before admission to (T1), and at the end of inpatient rehabilitation (T2; see Fig. 1). Questionnaires at T0 and T1 will be given online. At T2 questionnaires can also be administered in paper and pencil form. At T0 patient characteristics like family status and employment will be assessed together with the patient’s history of pre-treatment. Their Internet use will be ascertained as well. The following instruments are used at each time point. The short form of the Patient Health Questionnaire-4 (PHQ-4) [25] will be used to measure depression and anxiety. The mental condition will be assessed at each time point with the Indicators of Rehabilitation Status (IRES-24) [26]. Additionally, patients’ ability to work will be assessed with the Subjective Prognosis of Work Capacity (SPE) [27]. To measure the patient’s expectancies, the Credibility Expectancy Questionnaire (CEQ) [28] will be given at T0 and T1. Furthermore, the Work-Related Therapy Motivation Questionnaire (FBTM) [29], the Questionnaire for Assessment of Rehabilitation Expectancy and Motivation (FREM-17 [30]), and the Patient Questionnaire for Assessment of Rehabilitation Motivation-20 (PAREMO-20 [31]) will be used to assess work-related therapy motivation and treatment motivation at T0 and T1 as well. The use of the IP and websites with clinic reviews and ratings as well as the clinic websites will be measured only at T1. Patients will be asked about their satisfaction with inpatient treatment at T2. All questionnaires and the time points at which they are administered are displayed in Table 1.

**Fig. 1 Fig1:**
[figure not shown]
Study design and time points of assessment. *IG* intervention group, *CG* control group, *TAU* treatment as usual

**Table 1 Tab1:** Schematic overview of frequency and scope of the study visits

Visits/scope	First login on platform	After randomization	Before inpatient rehabilitation	End of rehabilitation
Study visits		T0	T1	T2
Written informed consent	X			
Internet use		X		
Pre-treatment		X		
CEQ		X	X	
FBTM		X	X	
FREM-17		X	X	
PAREMO-20		X	X	
PHQ-4		X	X	X
IRES-24		X	X	X
SPE		X	X	X
IP usage			X	
Use of websites with clinic reviews and clinic website			X	
BADO			X	X
Patient Satisfaction Questionnaire-8 (ZUF-8)				X

*BADO* Basis documentation

### Objectives and hypotheses

The primary objective of our trial is to determine the effect of our IP on participants’ outcome expectancy concerning inpatient psychosomatic rehabilitation. We hypothesize a more positive outcome expectancy measured with the CEQ in the intervention group than in the control group at T1. We further hypothesize that the intervention group will have a greater work-related therapy motivation measured with the FTBM than the control group at T1.

### Outcomes

The primary outcome in the study is the outcome expectancy (CEQ) measured at T1 (two weeks before admission to inpatient rehabilitation).

Key secondary outcomes are:Work-related therapy motivation (FBTM) at T1Treatment motivation (FREM-17 and PAREMO) at T1Treatment credibility (CEQ) at T1Satisfaction with and usage of IP at T1Mental condition (IRES-24) at T2 (end of rehabilitation)Satisfaction with inpatient rehabilitation (ZUF-8) at T2Subjective prognosis of work ability (SPE) at T2Depression and anxiety (PHQ-4) at T2Functioning in everyday life (IRES-24) at T2Perceived advantage of aftercare at T1 and T2

Predictors of outcome are:Therapy motivation (FREM-17 and PAREMO-20) at T0 (after randomization)Internet use and technology affinity at T0Use of websites with clinic reviews and ratings as well as use of the cooperating clinics’ websites at T1Previous, especially rehabilitation, treatments prior to the current inpatient rehabilitation at T0

We have defined four predictors of outcome which may have an additional impact on outcome, potentially confounding the impact of patients’ expectations. As it has a major influence on the therapy success, treatment motivation will be controlled [32]. We further think that strong Internet use and technology affinity may influence the use of our platform [33]. We will control for the use of websites with clinic reviews and ratings as well as the use of the cooperating clinics’ websites. Finally, we need to know if patients have had prior inpatient (rehabilitative) treatments, as previous experience may influence expectations. All predictors will be used as control variables in additional explorative analyses after testing our primary and secondary outcomes.

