## Methods/design

### Participants

All patients referred to inpatient rehabilitation in one of the three cooperating clinics who are more than 18 years old are eligible for study participation. They will receive the study information together with the usual clinic documents and information about inpatient rehabilitation. Together with the study information, each patient will additionally receive a personal code and a link to the Internet platform (IP). After logging into the IP, patients need to agree to the informed consent presented on the platform. Patients who give their informed consent will be randomized to the intervention or control group and will receive the first questionnaire immediately.

Furthermore, all patients who complete all three questionnaires are eligible to take part in a drawing after completing the third assessment. Patients participating in the drawing can win one of ten cash checks worth 50 € each.

Personal data will be stored at the Study Center of Mental Disorders at the University Medical Center of the Johannes Gutenberg-University Mainz and each cooperating clinic. However, the study assistants with access to the personal data will have no access to the research data collected using questionnaires. Administration of the IP will be managed only by research fellows of the Department of Psychosomatic Medicine and Psychotherapy of the University Medical Center Mainz and the study assistants in the cooperating clinics.

The clinical protocol and informed consent were approved by the Ethics Committee of the Federal State of Rhineland-Palatinate (Germany), which is responsible for the coordinating center in Mainz (Ref. Number 837.192.15 (9960)). Additional approval from Ethics Committees responsible for the cooperating clinics is not necessary if the documents submitted by the coordinating center have been approved by an Ethics Committee. All procedures described in the clinical trial protocol (ClinicalTrials.gov identifier: NCT02532881) follow the International Conference on Harmonization-Good Clinical Practice (ICH-GCP) guidelines and the ethical principles described in the current revision of the Declaration of Helsinki. The trial will be carried out in accordance with local legal and regulatory requirements. A SPIRIT checklist is provided as an additional file (see Additional file 1).

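### The explorative analyses plan to control for website use recorded only at T1, after randomization and during platform access, so an arm effect adjusted for it can be biased

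*Protocol article*

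**What the plan says.** The Outcomes section of the protocol article names four predictors of outcome. Three are dated T0: therapy motivation, Internet use with technology affinity, and previous treatment. The fourth, website use, is dated T1, and the section commits to adjusting for it: "We will control for the use of websites with clinic reviews and ratings as well as the use of the cooperating clinics’ websites". It closes with "All predictors will be used as control variables in additional explorative analyses after testing our primary and secondary outcomes". The reason given is that the predictors may affect outcome, "potentially confounding the impact of patients’ expectations".

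The Assessment section confirms that no baseline version exists: "The use of the IP and websites with clinic reviews and ratings as well as the clinic websites will be measured only at T1". Table 1 agrees, with a single mark under T1.

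On timing, the Participants section says "Patients who give their informed consent will be randomized to the intervention or control group and will receive the first questionnaire immediately", and the Intervention section says "Participants of the intervention group will get access to the IP after they have given their informed consent" and that access ends at admission. T1 falls two weeks before admission.

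The Statistical methods section defines the primary analysis as an ANCOVA of CEQ at T1 with CEQ at T0 as the covariate. The first eight secondary outcomes are analysed in the same way.

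**The concern.** Randomization protects the arm comparison against confounding by anything that precedes it. A variable recorded weeks into the exposure period is not of that kind, because allocation may have changed it. The platform gives information about rehabilitation, and usual preparation already includes a link to the clinic homepage. Patients with the platform might therefore search elsewhere less (substitution) or more (prompting).

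If so, adjusting for website use does one or both of two things:

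- It removes the part of the platform's effect that runs through searching (mediator).
- It opens a non-causal path through whatever drives both searching and expectancy, such as general engagement (collider).

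The adjusted coefficient then no longer estimates the effect of offering the platform, which is the primary objective. The models are motivated by possible confounding, so a coefficient that differs from the primary result could be read as a correction of it.

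**Working it through.** The plan states no figure on this point, so there is none to reproduce. The check is one of timing, followed by an illustration.

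**1. Timing**

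| Event | When | Source in the article |
|---|---|---|
| Randomization | at consent, first login | Participants |
| T0 questionnaire | immediately afterwards | Participants; Table 1 |
| Platform opens (intervention arm) | after consent | Intervention |
| Website use recorded | T1 only | Assessment; Table 1 |
| Primary outcome (CEQ) | T1 | Outcomes |
| Platform closes | admission | Intervention |

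Website use is therefore recorded after randomization, inside the exposure window, and together with the primary outcome.

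**2. What adjustment does to an arm effect**

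Let A be arm, W website use (within-arm SD 1), U an unmeasured shared cause such as engagement (SD 1), and Y the outcome:

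- W = a·A + g·U + error
- Y = τ·A + b·W + h·U + error

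The total effect of arm is τ + a·b. Within arm, the slope of Y on W is b + g·h. The arm coefficient after adjusting for W is therefore

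adjusted = total − a·(b + g·h).

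The total is set at 0.24, the effect size in the Sample size calculation section. The values of a, b, g and h are assumptions, since the article gives none.

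| Scenario | a | b | g, h | Arithmetic | Adjusted effect |
|---|---|---|---|---|---|
| Arm does not change use | 0 | 0.2 | 0.4, 0.4 | 0.24 − 0 | 0.24 |
| Shared cause only | ±0.3 | 0 | 0.4, 0.4 | 0.24 ∓ 0.3 × 0.16 | 0.19 or 0.29 |
| Mediator only | ±0.3 | 0.2 | 0, 0 | 0.24 ∓ 0.3 × 0.20 | 0.18 or 0.30 |
| Both | ±0.3 | 0.2 | 0.4, 0.4 | 0.24 ∓ 0.3 × 0.36 | 0.13 or 0.35 |

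Simulation with 2,000,000 patients agrees: 0.238 in the first row, then 0.191 and 0.288, 0.181 and 0.300, 0.130 and 0.349. Without W in the model, the estimate is 0.24 up to simulation error in every row.

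**3. Effect of T0 covariates**

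The explorative models would also contain T0 variables. Take the shared-cause-only row and add one T0 covariate X, correlated 0.6 with the outcome and r with U (again assumptions). The slope on W becomes (g·h − 0.6·g·r) / (1 − g²r²).

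- r = 0.4: (0.16 − 0.096) / (1 − 0.0256) = 0.066. Shift 0.3 × 0.066 = 0.02; adjusted effect 0.22 or 0.26.
- r = 0.6: (0.16 − 0.144) / (1 − 0.0576) = 0.017. Shift 0.3 × 0.017 = 0.005; adjusted effect 0.235 or 0.245.
- r = 0: slope 0.16; adjusted effect 0.19 or 0.29, as before.

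T0 covariates can therefore remove much or little of the collider part, depending on how well they capture the shared cause.

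**4. If the target is the impact of expectations**

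Here T1 expectancy is the explanatory variable, and website use is recorded at the same visit. Reading reviews may shape expectancy, or expectancy may lead patients to look things up. One simultaneous measurement cannot tell these apart, so the role of prior confounder is assumed, not established.

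**The case against.** Four points can be made in defence of the plan.

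*The arm effect is not named as the target.* This stands. The stated rationale concerns the impact of expectations. Reading the models as adjusted arm comparisons is a fair inference, because they follow arm-comparison ANCOVAs, but it is an inference. Under the other reading, website use could be a genuine confounder for some patients; what fails is the assumption that it is one.

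*Nothing shows that allocation changes website use.* This also stands. Both arms receive the usual preparation with the homepage link, and with no arm effect on use there is no bias. The plan cannot know this in advance, however, and the adjustment is fixed regardless.

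*Any size is assumed, and T0 covariates may absorb much of it.* This stands, as step 3 shows. A reader might infer a percentage bias from the table; the documents support none.

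*The analyses are only explorative.* True, and it limits the consequences. A reader might infer that the primary result is compromised. It is not, since that model contains only CEQ at T0 beside arm.

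Two further inferences should be resisted. The article says "strong Internet use and technology affinity may influence the use of our platform", which may suggest that Internet use belongs in the plan only as a moderator. A baseline trait can be both covariate and moderator, and adjusting for it does not bias the arm effect. Table 1 also places T0 after randomization, which may suggest that no predictor is usable. The T0 questionnaire is given immediately, so its exposure to the platform is not comparable with that of T1. The order of T0 and randomization is a separate procedural matter.

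**Conclusion.** The point holds in a limited form. The article states both the adjustment and the T1-only measurement, and its timeline places that measurement after randomization and during exposure. An explorative arm effect adjusted for website use can therefore be biased upward or downward. This depends on allocation changing website use, and on use either affecting the outcome or sharing an unmeasured cause with it. The size cannot be determined from the documents: 0.13 to 0.35 around 0.24 illustrates one set of assumptions, and zero bias is equally compatible with the text. If the target is the impact of expectations, the weakness is the unsupported assumption that website use precedes expectancy. The primary and secondary ANCOVAs and the sample size are unaffected.

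**What to change.** In the Outcomes section, restrict the control variables in explorative models of the arm effect to the three T0 predictors: therapy motivation, Internet use with technology affinity, and previous treatment. Report T1 use of review sites and clinic websites by arm as a descriptive process outcome, or analyse it in a mediation analysis declared as such. If a model of the impact of expectations is intended, say so separately and do not present T1 website use there as an established prior confounder.

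The cost is a change of wording, with no new data and no change in sample size. The explorative models lose one predictor and no longer address website use by adjustment.

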### Statistical methods

Analysis of covariance will be used to evaluate the CEQ scores at T1 between the intervention and control groups with CEQ score at T0 as the covariate. The first eight secondary outcomes will be analyzed with analyses of covariance in analogy to the primary outcome. The last two secondary outcomes will be reported with descriptive statistics. Intention-to-treat analyses with multiple imputations to replace missing data as well as per-protocol analyses will be conducted.

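### The confirmatory ANCOVAs adjust only for the outcome's own T0 score and leave prior treatment and T0 motivation to explorative models, forgoing a modest precision gain, most relevant for ZUF-8 and the other T2 outcomes

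*Protocol article*

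**What the plan says.** Statistical methods (protocol article) fixes the primary comparison of CEQ at T1 "between the intervention and control groups with CEQ score at T0 as the covariate". It continues: "The first eight secondary outcomes will be analyzed with analyses of covariance in analogy to the primary outcome".

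Outcomes lists four predictors of outcome, among them T0 motivation (FREM-17 and PAREMO-20) and previous treatment. Two reasons are relevant here. On motivation: "As it has a major influence on the therapy success, treatment motivation will be controlled". On earlier inpatient or rehabilitative treatment, the plan wants to know about it "as previous experience may influence expectations". The section then assigns all four a place outside the main tests: "All predictors will be used as control variables in additional explorative analyses after testing our primary and secondary outcomes".

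Table 1 shows FREM-17, PAREMO-20 and the pre-treatment history collected at T0. ZUF-8 appears there at T2 only. On the order of events, Participants says that consenting patients "will be randomized to the intervention or control group and will receive the first questionnaire immediately".

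**The concern.** In a randomised comparison, a prognostic baseline variable earns its place through precision: it takes explained variance out of the error term. Here two variables that the plan itself regards as prognostic are collected before outcome assessment, yet they are absent from the models that carry the conclusions. An explorative model run afterwards does not give that precision back to the confirmatory test.

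ZUF-8 sharpens the point. It is among the eight outcomes to be analysed like the primary one, but it has no T0 measurement, so the rule gives it no baseline covariate.

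The planned explorative model is also a poor substitute. It takes in all the predictors, including website use measured at T1. That is a post-randomisation variable which the intervention could change, so the resulting estimate is not a clean covariate-adjusted treatment effect.

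**Working it through.** **1. The plan's own figure.** Sample size calculation gives d = 0.24, significance level 0.05, power 0.80, one covariate, two groups and N = 788. For an ANCOVA, f = d/2 and the noncentrality is λ = N·f², with 1 and N − 3 degrees of freedom.

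- d = 0.24 (f = 0.12): the required N is 547, not 788. At N = 788, λ = 788 × 0.0144 = 11.35 and power is 0.920.
- d = 0.20 (f = 0.10): the required N is 787, or 394 per arm after rounding up. At N = 788, λ = 7.88 and power is 0.801. The 2459 patients to be approached also match 787/0.32 = 2459.4.

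The stated inputs therefore do not reproduce 788. That section needs reconciling in its own right; here both effect sizes are carried forward.

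**2. What added covariates would buy.** Let R² be the share of the variance left after the T0 score that prior treatment and T0 motivation explain. The protocol gives no value, so 2–10% is an assumption. The SE factor is √(1 − R²), and the equivalent sample size is 788/(1 − R²). Power uses λ = 788·f²/(1 − R²) and, allowing five covariate degrees of freedom in total, 788 − 2 − 5 = 781 residual degrees of freedom.

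| Added R² | SE factor | SE reduction | Equivalent N (extra) | Power, d = 0.20 | Power, d = 0.24 |
|---|---|---|---|---|---|
| 0 | 1.000 | – | 788 | 0.801 | 0.920 |
| 0.02 | 0.990 | 1.0% | 804 (16) | 0.808 | 0.925 |
| 0.05 | 0.975 | 2.5% | 829 (41) | 0.820 | 0.932 |
| 0.10 | 0.949 | 5.1% | 876 (88) | 0.840 | 0.944 |

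**3. Where the primary outcome is likely to fall.** T0 CEQ is already in the model, so only what motivation adds beyond it counts. With b = corr(T0 CEQ, T1 CEQ), m = corr(T0 motivation, T1 CEQ) and i = corr(T0 motivation, T0 CEQ), the partial R² is [(m − b·i)/√((1 − b²)(1 − i²))]². The assumed values are b = 0.5, 0.6, 0.7; m = 0.2, 0.3, 0.4; i = 0.3, 0.5.

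- Highest of the 18 combinations (b = 0.5, m = 0.4, i = 0.3): [0.25/√(0.75 × 0.91)]² = 0.092.
- Lowest (for example b = 0.6, m = 0.3, i = 0.5): the numerator is 0.3 − 0.3 = 0, so the gain is nil.
- Nine of the 18 give 0.017 or less.

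The range is about 0.00–0.09, with half the combinations below the 2% row of the table.

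**4. Outcome by outcome.** The first eight secondary outcomes, in the order listed, are FBTM, FREM-17/PAREMO, CEQ credibility, platform satisfaction and usage, IRES-24 mental condition, ZUF-8, SPE and PHQ-4.

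- FREM-17/PAREMO: the analogous model already uses its own T0 motivation score.
- IRES-24, SPE and PHQ-4 at T2: each has a T0 score, but neither prior treatment nor motivation is in the model. The plan's claim about motivation concerns therapy success, so it bears most directly here.
- ZUF-8: no T0 score, hence no covariate under the rule.
- Platform satisfaction and usage also lack a T0 score, but only the intervention arm is given platform access, so covariates are not the issue there.

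**5. Is T0 a true baseline?** T0 follows randomisation, and Intervention says access opens after consent without placing it before or after the T0 questionnaire. Prior treatment is a historical fact and little exposed to this. T0 motivation is safe only if answered before the videos open. The same caveat applies to T0 CEQ, which the plan already uses.

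**The case against.** The strongest reply is that nothing here is wrong. The one-covariate ANCOVA is pre-specified, unbiased under randomisation, adjusted for the outcome's own earlier score, and consistent with a power calculation that assumes one covariate. The plan introduces the predictors because they may confound the effect of expectations, which is a different question from the randomised contrast, and explorative models suit that purpose. All of this stands: the point is about efficiency only.

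Several stronger readings are tempting, and the text does not bear them out:

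- **That the plan calls both variables strong influences on expectations and then ignores them.** The strong wording is about motivation and therapy success. On expectations, the text says only that previous experience may matter, and gives no strength.
- **That every main ANCOVA omits T0 motivation.** The FREM-17 and PAREMO analyses include it by construction.
- **That the imputation loses these variables.** An imputation model can contain variables that the analysis model does not, and the article does not describe its contents.
- **That the plan leaves two answers to choose between.** Outcomes fixes the order: main tests first, adjusted models afterwards as exploration.
- **That these are the only covariates open to ZUF-8.** CEQ, PHQ-4, IRES-24 and SPE are also collected at T0.

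It is also fair to say that the gain may be negligible for the primary outcome. FREM-17 itself assesses rehabilitation expectancy as well as motivation, so overlap with T0 CEQ is plausible.

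**Conclusion.** The point holds as a modest efficiency improvement. The planned analysis is valid and introduces no bias; a reader who inferred an error or a self-contradiction would be going beyond the text. Two T0 variables that the plan itself names as predictors are kept out of the confirmatory models, apart from motivation in its own analyses.

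For the primary outcome the gain is small: at most about 4 power points at d = 0.20 and about 2 at d = 0.24, and probably less. This rests on an assumed added R² of 2–10% and on the assumed correlations above; the protocol supplies neither. The case is better for the T2 outcomes, where the plan's own claim about motivation applies. It is clearest for ZUF-8, where the stated rule cannot be followed as written because there is no T0 score.

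**What to change.** - Pre-specify prior inpatient or rehabilitation treatment (yes/no) as a covariate in the primary and secondary ANCOVAs, alongside the outcome's T0 score where one exists.
- Add T0 FREM-17 and PAREMO-20, provided the T0 questionnaire is completed before the videos open. State that order explicitly.
- Name these variables as the baseline covariates for ZUF-8.
- Include them in the imputation model.
- Keep the T0-score-only ANCOVA as a sensitivity analysis.
- Do not extend the confirmatory adjustment to website use at T1.

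The cost is analysis-plan wording and no new data. With one score per motivation instrument, the models spend 1 + 2 = 3 further degrees of freedom out of 788 − 3 = 785; using subscales would take somewhat more.
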